**Procedures for handling missing, rejected and abnormal data**

If there is missing data on the primary endpoint, the patient's data will be excluded from the analysis. If it is found that missing data exists in the secondary evaluation item during data analysis, the item is treated as a deletion value and data analysis is performed.

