**4. [Research method and period]**

① Research implementation period

From November 1, 2017 to March 31, 2021.

② Information on drugs used

Name: Tsumura Yokukansan (Product number: 054)

Route of administration, dosage and administration: Oral, 1 packet (2.5 g) at a time

Dosage form: Extract granules

③ Research subjects

Patients aged 20 to 60 years who undergo breast cancer surgery at Niigata University Medical and Dental Hospital or Niigata Prefectural Cancer Center Niigata Hospital and undergo total mastectomy and sentinel lymph node biopsy, or partial mastectomy and sentinel lymph node biopsy (Details will be described later).

④ Research method

Multicenter / Open Label / Superiority test by forced random sampling

[1] A pre-treatment questionnaire survey will be conducted on all subjects, and the age, BMI, surgical history, and general status (American Society of Anesthesiologists-Physical Status: ASA-PS, ECOG-PS) will be recorded in advance. Also, before taking the study drug, record the measurement of amylase in saliva, the Hospital anxiety and depression scale (HADS), and the State Trait Anxiety Inventory (STAI).

[2] Subjects are assigned to two groups, one with yokukansan (intervention) and the other without (control), according to the results of randomization. The intervention group should be given 1 packet (2.5 g) of TSUMURA Yokukansan before sleep on the day before surgery and 1 packet (2.5 g) 2 hours before entering the operating room on the day of surgery. For the purpose of maintaining the same quality between the two groups, a forced allocation algorithm is created, and if a bias is confirmed between the groups, forced allocation is performed based on age, surgical history, etc.

[3] Subjects in the intervention group take 1 packet of yokukansan orally 2 hours before entering the operating room on the day of surgery, and then all participants are measured salivary amylase in the operating room. Anesthetized by general anesthesia in the operating room and undergo total or partial mastectomy and sentinel lymph node biopsy

[4] Record salivary amylase measurements, HADS, STAI, visual analog scale of pain: VAS, QOR (Quality of recovery), and the presence or absence of analgesic use 24 hours after surgery.

| 24-hour before surgery | Salivary amylase  HADS STAI |
| --- | --- |
| Just before surgery | Salivary amylase |

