| 24-hour after surgery | Salivary amylase  HADS STAI  Visual analog scale for postoperative pain  QOR  Rescue analgesics usage |

※The allowable range is ± 12 hours before and 24 hours after surgery.

⑤ Sample size

In this study, we plan to perform Bayesian analysis. In this method, the posterior probability of the response rate is calculated by an interim analysis, and the calculated posterior probability is monitored. If it is judged that the effect is not as good as that of untreated, the test should be discontinued. Is planned. In addition, since the posterior predictive distribution is obtained based on the data obtained from the interim analysis, it is possible to judge whether the additional data follows the distribution, and it is possible to save the number of cases by performing this procedure. Is known to be. As an interim analysis, an exploratory analysis will be performed when 20 cases in a group are reached based on reference [1]. Recalculate the required number of cases based on the results of the interim analysis. Regarding the design of the number of cases, referring to the previous study, 1-β was 80%, the significance level was 0.05, and the success rate of the intervention group (yokukansan was expected to be taken preoperatively and preoperatively: impression at the outpatient clinic of pain clinic) is set to 75%. About 40 cases are expected in each group. The clinically meaningful difference is defined as σ = 0.3.

[1]Young-Chang Arai, et al, Evidence based Complementaly and Alternative Medicine.2014; ID965045

⑥ Study endpoints

Primary endpoint: Salivary amylase level

Secondary endpoint: HADS STAI QOR Pain VAS

⑦ Analysis method

Statistical analysis methods are planned to be performed by the maximum likelihood estimation method and the Bayesian statistical method. All analysis is performed by a person in charge of analysis different from that of the principal investigator.

For maximum likelihood estimation methods, t-tests that do not correspond to continuous variables, Fisher's exact test for scale classification, and Mann-Whitney U test for continuous variables or ordinal variables that do not follow a normal distribution such as VAS. A test will be used to determine P <0.05 as significant.

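### As worded, a missing salivary amylase value excludes the patient, so read literally it also discards that patient's valid pain VAS, HADS, STAI and QOR results

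*Protocol*

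**What the plan says.** The section on missing, rejected and abnormal data, which follows Protocol section 12, sets two rules. For the primary endpoint: "If there is missing data on the primary endpoint, the patient's data will be excluded from the analysis". For a missing secondary item: "the item is treated as a deletion value and data analysis is performed". The first rule acts on the patient, the second on the item.

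Section 4 ⑥ defines the endpoints as "Primary endpoint: Salivary amylase level" and "Secondary endpoint: HADS STAI QOR Pain VAS". The primary endpoint carries no time point.

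Section 4 ④ schedules three amylase measurements:

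- at baseline ("before taking the study drug, record the measurement of amylase in saliva");
- just before surgery ("all participants are measured salivary amylase in the operating room");
- 24 hours after surgery, together with the questionnaires and the pain score ("Record salivary amylase measurements, HADS, STAI, visual analog scale of pain: VAS, QOR (Quality of recovery").

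The same section describes the trial as open label.

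**The concern.** HADS, STAI, QOR and pain VAS are obtained without saliva, so they can be complete and valid when a saliva sample is not. A rule that removes the patient because amylase is missing throws those results away for a reason unrelated to them. Pain is in the trial's title, and section 3 states that no clinical study has examined yokukansan for postoperative pain. The data at risk therefore bear on one of the trial's two stated questions.

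Two things are at stake. The first is precision on every secondary endpoint. The second is selection. The operating-room and 24-hour samples come after allocation, and patients and staff know the allocation. Conditioning the secondary comparisons on successful sampling at those times is a post-randomisation selection. It would bias them if failure differed by arm or was related to anxiety. A missing baseline sample does not raise this problem in the same way, because it precedes study drug.

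**Working it through.** **Scope of the rule.** The two sentences sit side by side and use different units: the patient's data for a missing primary value, the item for a missing secondary value. If both were meant at the level of the endpoint, the different units would be unnecessary. No other section restricts the first rule to the amylase analysis or keeps such patients for the secondary endpoints. Patient-level exclusion is therefore the more literal reading, though not the only possible one.

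**The plan's own size.** Section 4 ⑤ gives "1-β was 80%, the significance level was 0.05", an intervention success rate of 75%, a meaningful difference written as σ = 0.3, and about 40 per group. Reading 0.3 as a difference in proportions (an assumption) gives 45% in controls. With a two-sided pooled test and no continuity correction:

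n = [1.960·√(2·0.60·0.40) + 0.842·√(0.75·0.25 + 0.45·0.55)]² / 0.30² = (1.358 + 0.555)² / 0.09 ≈ 40.7, so 41 per group.

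This agrees with about 40, so 40 per group is the starting point. Section 4 ⑤ states no allowance for exclusions.

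**Cost of the rule.** Let p be the failure rate per saliva sample, taken as equal in both arms. The protocol gives none, so p = 3%, 5% and 10% are assumptions.

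- One sample defines the endpoint: n left = 40(1−p); standard-error ratio = (1−p)^(−1/2).
- Any of three independent failures triggers exclusion: n left = 40(1−p)³; standard-error ratio = (1−p)^(−3/2).

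| p | One sample: n left | SE ratio | Any of three: patients lost | n left | SE ratio |
|---|---|---|---|---|---|
| 3% | 38.8 | 1.015 | 8.7% | 36.5 | 1.047 |
| 5% | 38.0 | 1.026 | 14.3% | 34.3 | 1.080 |
| 10% | 36.0 | 1.054 | 27.1% | 29.2 | 1.171 |

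If failures cluster within patients, the any-of-three loss is smaller. With complete clustering it falls to p, the one-sample case. The two sets of columns therefore bracket the range from full clustering to independence.

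**In terms of power.** The protocol claims no power for the secondary endpoints. As a reference, take the standardised effect that would have 80% power with 40 per group: (1.960 + 0.842)·√(2/40) = 0.626. At 5% and 10% failure, power for that effect is 78% and 76% if one sample counts, and 74% and 67% if any of three counts. With the exclusion limited to amylase, a failed saliva sample costs the secondary analyses no patients and the reference power stays at 80%.

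**The case against.** The strongest reply is that the text speaks of the analysis, not of all analyses. The sentence opens with the primary endpoint and the next turns to secondary items, so it may have been meant for the primary analysis only. The English is rough enough that fine distinctions of wording carry limited weight. This stands as a caveat. A reader might infer that the protocol definitely removes such patients from every analysis; the text does not go that far. But nothing confirms the narrower meaning either, and leaving it open lets the choice be made after the data are seen.

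A reader might also infer that one failed sample of three is enough for exclusion. The protocol does not say so, because the primary endpoint names no time point. The any-of-three figures are the upper case, and independence between samples sits awkwardly with the idea that failure reflects a patient trait such as anxiety.

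A third inference is that samples fail differently by arm because controls have nothing by mouth two hours before surgery. Section 9 says only that controls take no medication; it mentions neither water nor fasting. Differential failure is a possibility that the rule exposes the trial to, not something the documents show.

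Finally, the harm falls on secondary endpoints for which no power is claimed, and the primary comparison cannot use a missing amylase value under either wording. That is correct and limits the weight of the point. It does not justify discarding valid data.

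**Conclusion.** The point holds as a defect in a stated rule. Taken literally, and against its own contrast between patient and item, it removes valid secondary results because a different measurement is missing, and no other section narrows it. Over the assumed 3% to 10% failure per sample, the secondary analyses lose 3% to 10% of patients (standard error up about 1.5% to 5.4%) if one sample defines the endpoint. If any of three independent failures triggers exclusion, they lose 8.7% to 27.1% (standard error up about 5% to 17%). These sizes rest on assumed failure rates, equal loss in the two arms and, for the upper range, independence. Bias is possible but not demonstrated. The change is worth making because the loss serves no purpose for the secondary endpoints and is cheap to avoid.

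**What to change.** Replace the first sentence of the missing-data section with wording such as: *A missing salivary amylase value removes the patient only from the amylase analysis at that time point; patients otherwise retained in the study are analysed for every secondary endpoint and amylase time point for which they have a value.* Report the number of missing saliva samples by arm and time point.

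The restriction to patients otherwise retained is needed. Section 5(3) lists cancellation criteria, section 5(4) excludes certain patients who withdraw, and section 12 discards data already collected when participation ends. The sentence must be read together with those rules and does not change them. Promising analysis of every randomised patient would contradict them.

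The cost is one sentence and no new data. Numbers analysed will differ slightly between endpoints, so each result should carry its own denominator. The amylase analysis itself remains complete-case; the change does not address any non-random loss there.

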**13. [Contents and methods of reporting to the director of the research institution]**

If we obtain facts or information that impair the ethical validity or scientific rationality of the research, or facts or information that may impair the appropriateness of the research implementation or the credibility of the research results, promptly document the relevant matters and countermeasures. Report. If we become aware of a serious adverse event, we will promptly report it in writing. At the end of the study, report the study results in writing without delay.

**14. [Status of conflicts of interest related to research by research institutes, such as funding sources for research, and conflicts of interest related to research by researchers, etc.]**

① How to raise research funds

Plan to use basic expenses such as university operating expenses in the field of anesthesiology

(2) Items to be confirmed regarding conflicts of interest

None

**15. [Method of disclosing information on research]**

The results of this research will be published by presenting them at academic meetings such as academic societies and academic journals. The outline of this study will be registered in the UMIN clinical trial registration system, which is a public database, before the start of the study, and the registered contents will be updated according to changes in the research plan and the progress of the study. When the research is completed, the results of the research will be registered. The outline, progress, results, etc. of clinical research will be announced on jRCT (<https://jrct.niph.go.jp/>).

**16. [Responding to consultations, etc. from research subjects and related parties]**

Not listed for personal information protection

-------------------------------------------------------------------------------------------------------

**Check the following whether it is applicable or not, and if applicable, describe the details.**

**17. [When receiving informed consent from a surrogate, etc.]**

□ Applicable ・ ■ Not applicable

**18. [When obtaining informed assent]**

□ Applicable ・ ■ Not applicable

**19. [When conducting research in a situation where the research subject is in an urgent and obvious life-threatening situation]**

□ Applicable ・ ■ Not applicable

20. [When the research subject has an economic burden or a reward]

□ Applicable ・ ■ Not applicable

**21. [For studies involving invasive procedure ①]**

■ ︎ Applicable ・ □ Not applicable

This study is not covered by clinical research insurance and does not provide any other compensation. In the event of a health hazard, the investigator will deal with it in good faith and provide appropriate medical care. The cost will be covered by the subject's insurance, and no special compensation will be provided by this study. Explain the above points to the subjects in advance and obtain their consent.

**22. [In the case of research involving invasive procedure ②]**

■ ︎ Applicable ・ □ Not applicable

Hypokemia, gastrointestinal disorders (diarrhea and nausea), and liver dysfunction have been reported as adverse events, but the frequency is stated to be less than 0.1 to 5% in the attached text, all of which are long-term. It is a side effect of continuous use (reported in 13 days at the earliest). Most of them occur in the elderly aged 65 and over. Since this time, the drug was taken only twice, it is highly unlikely that such side effects will occur. In the unlikely event that yokukansan causes health problems, the researcher will deal with it in good faith and provide appropriate medical care. The cost will be covered by the subject's insurance, and no special compensation will be provided by this study.

**23. [In the case of research involving medical practice beyond normal medical care]**

□ Applicable ・ ■ Not applicable

**24. [When there is a possibility that important findings regarding the health of the research subject, genetic characteristics that can be inherited by offspring, etc. may be obtained by conducting the research]**

□ Applicable ・ ■ Not applicable

**25. [When entrusting a part of research-related work]**

□ Applicable ・ ■ Not applicable

**26. [Possibilities for future use of acquired samples and information]**

■ Applicable ・ □ Not applicable

There is a possibility of performing secondary analysis.

**27. [Procedures for monitoring and auditing]**

■ Applicable ・ □ Not applicable

The person in charge of monitoring will investigate that this study is being carried out properly at this hospital, that necessary items are accurately recorded, and that the reliability of the data is sufficiently maintained. If any matter that affects the proper implementation of this research or deviation from the research plan is confirmed, the matter is promptly notified to the principal investigator and the research institution as necessary, and they are reported. Appropriate measures shall be taken to prevent the recurrence of the matter.

The person in charge of audit evaluates the implementation of this research including monitoring and the status of compliance with the ethical guidelines and research implementation plan from an objective standpoint, and conducts the audit.
